#### Subgroup analysis

Exploratory subgroup analyses of the following possible interactions will be undertaken to assess whether the effect of sociotherapy intervention is modified by the prespecified covariates: survivors, perpetrators, and youth. These subgroup analyses will be performed by adding the interaction term between the allocated group and the subgroup variable into the generalized effect model. Given the limited power to detect treatment–subgroup interactions, analyses of the results will be interpreted with caution. All subgroups will be analyzed using the intention to treat the population. Wherever applicable, to compensate for multiple comparisons, this study will employ a Bonferroni correction factor.

#### Interim analyses

No formal interim analysis will be conducted on the primary and secondary outcomes. However, data monitoring will be done to ensure that the data collected are in the right format at baseline and at both endlines. This will be conducted by UR researchers, who are performing an external evaluation.

## Methods in analysis to handle protocol non-adherence and any statistical methods to handle missing data

The reasons for missing data will be reported and if missing data is < 5%, multiple imputation will be used to handle missing data [48] using SPSS (version 28).

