### Sample size

The sample size was estimated based on pilot study results. As there was no similar previous study allowing to asses intraclass correlation, the authors of this study have conducted a pilot study on a sample of 559 people. The objectives of the pilot study were (1) to test the psychometric properties of the Social Dignity Scale and (2) to assess potential Intra-CBS groups correlation. The results from the pilot study revealed an intraclass correlation of 0.15. The targeted treatment effects were established in terms of clinical judgment, not through the pilot of data [37]. According to previous CBS experience, an average of 3 out of 15 participants in a CBS group dropout the intervention without achieving at least 11/15 required sessions. All enrolled CBS groups are facilitated to the end of the intervention. Considering an intraclass correlation coefficient, Rho = 0.15 and a standard Alpha = 0.05, an a priori power calculation using the Optimal Design Software [38] revealed that 80 CBS groups (40 control and 40 intervention) composed of 12 participants each group would make it possible to achieve the standard power of 0.80 while detecting a small Cohen’s *d* effect size of 0.3. The required total sample was then found to be 960 (i.e., 12 × 80) participants. However, assuming a minimalistic response rate of 96% according to a previous similar social study in Rwanda evidencing that it ranges from 96% [39] to 99.8% [40], we would need to recruit 1000 participants. To provide a buffer against potential attrition-related problems, at least 15 recruited beneficiaries of CBS that fulfil the inclusion criteria will be included in the study making the final sample size to recruit up to 1200 participants.

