### Plans to promote participant retention and complete follow-up

No additional strategies will take place to improve retention and completion by participants in this trial, in keeping with the ecological design of this study.

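### The missing-data rule appears reversed: multiple imputation is specified only below 5% missing, and no method is stated for 5% or more, a level the sample size provides for

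*Protocol article*

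**What the plan says.** The section on non-adherence and missing data says that reasons for missing data will be reported and that "if missing data is < 5%, multiple imputation will be used to handle missing data", in SPSS. It gives no method for 5% or more. It also does not say whether the limit applies overall, per arm or per variable. No other section covers missing outcome data.

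The Sample size section contains three separate statements about loss:
- On attendance, earlier CBS experience is that "an average of 3 out of 15 participants in a CBS group dropout the intervention without achieving at least 11/15 required sessions".
- On survey response, the required 960 is raised to 1000, "assuming a minimalistic response rate of 96% according to a previous similar social study in Rwanda".
- On attrition, the text continues: "To provide a buffer against potential attrition-related problems, at least 15 recruited beneficiaries of CBS" who meet the criteria will be included, "making the final sample size to recruit up to 1200 participants".

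The Primary analysis section declares intention to treat and puts the change in social dignity, from baseline to each endline separately, into a GEE model as the dependent variable. The baseline score is a covariate. Mixed-effects regression and a t-test are listed as robustness checks. The section on retention says: "No additional strategies will take place to improve retention and completion by participants in this trial".

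**The concern.** A threshold of this kind normally runs the other way: a simple analysis is tolerated when very little is missing, and a principled method is required when more is. As written, the rule requires imputation when its effect would be small and provides nothing once missingness could influence the result.

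The primary outcome is a change score, so a participant without an endline score has no outcome value for that comparison. If nothing is imputed, the GEE would by default drop that person. Some reasons for leaving exist only in the CBS arm: only those participants attend sessions, and only they can be discontinued for not complying with group rules. Loss to the surveys could therefore differ by arm and be related to outcome. A comparison of those who remain would then no longer be the comparison of everyone randomised that intention to treat promises. With no method fixed at 5% or more, the choice could also be made after the data have been seen.

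**Working it through.** **Inputs (Sample size section unless noted).** 80 CBS groups, 40 per arm; 12 analysed and 15 recruited per group; ICC 0.15; alpha 0.05 (two-sided assumed, since the article does not say); d = 0.3; power 0.80; response rate 96%; session dropout 3 of 15. The 5% limit comes from the missing-data section.

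**1. The plan's own figures reproduce.**
- Noncentrality: λ = J·d² / {4[ρ + (1 − ρ)/n]} = 80 × 0.09 / {4 × [0.15 + 0.85/12]} = 7.2 / 0.883 = 8.15. With an F(1, 78) reference, power is 0.805, against the stated 0.80.
- Cross-check: design effect 1 + 11 × 0.15 = 2.65. With 175 per arm under individual randomisation, the total is 2 × 175 × 2.65 = 928, just below 960.
- Non-response: 960 / 0.96 = 1000.
- Final sample: 80 × 15 = 1200.

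**2. The loss the design provides for.** 1 − 960/1200 = 20%. The step from 960 to 1000 already covers 4% non-response. The further 200 are therefore provision for loss beyond that.

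**3. Where the rule stops.** Read as an overall limit, 5% of 1200 is 60 people, so the rule applies only while fewer than 60 are missing.

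| Scenario | Missing of 1200 | Share | Method stated? |
|---|---|---|---|
| Non-response at the stated 96% | 48 | 4% | Yes |
| 12 more missing records | 60 | 5% | No |
| 3 of 15 unsurveyed, CBS arm only (40 × 3) | 120 | 10% | No |
| 3 of 15 unsurveyed, both arms (80 × 3); the whole buffer used | 240 | 20% | No |

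The last two rows are scenarios, not forecasts. The 3 of 15 describes session attendance and becomes missing outcome data only if those people are also not surveyed.

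**4. Effect on power.** Spreading the loss evenly over groups, power is 0.826 at 4% loss (14.4 per group), 0.819 at 10% (13.5 per group) and 0.805 at 20% (12 per group). The design tolerates these losses in precision. What is left open is the method of analysis and the possible bias.

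**The case against.** The strongest reply is that the only survey figure in the plan, 4% non-response, lies inside the rule, so the gap may never be reached. The buffer is a precaution and not a prediction, and the fault may be no more than a reversed inequality sign. All of this is fair. It does not rescue the rule, because the margin is 12 people and the design deliberately provides for larger losses.

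A second reply is that the detail belongs in the SAP. That holds for the list of imputation variables, imputation by arm and similar choices. It does not hold for the trigger, which is stated in the article. A SAP that follows it inherits the error, and one that departs from it contradicts the published plan.

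Four stronger readings are tempting, and the document does not support them:
- *A reader might infer that the plan expects 20% missing outcomes.* The 3 of 15 are people who do not reach 11 of 15 sessions. Nothing says they will go unsurveyed, and under intention to treat they should be surveyed. Adding this figure to the 4% would combine two different quantities.
- *A reader might infer that the plan adopts an available-case analysis and so contradicts intention to treat.* No section says so. It is the default behaviour of the named model, and the text is silent.
- *A reader might infer that retention efforts are ruled out.* Only additional strategies are excluded. The adherence section keeps face-to-face follow-up and encouragement by facilitators, which are aimed at session attendance.
- *A reader might attach a size to the bias.* For example, 20% of the CBS arm unmeasured and scoring 0.3 to 0.5 SD lower gives 0.20 × 0.3 to 0.5 = 0.06 to 0.10 SD, or 20% to 33% of d = 0.3. That assumes every session dropout is unmeasured, assumes a gap the document does not give, and assumes the baseline covariate removes none of it.

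**Conclusion.** The point stands as an error in a stated rule. Multiple imputation is tied to the wrong side of the 5% limit, and no method is given for 5% or more, although the sample size leaves room for up to 20% loss. The consequence is an unspecified method for the intention-to-treat primary analysis at those levels, with possible bias if loss differs by arm and is related to outcome. The direction and size of any bias cannot be derived from the document. Power is not at stake.

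The conclusion assumes that the limit is read as an overall proportion of participants, and that the GEE handles missing change scores in its usual way. If the limit were applied per arm, it would be 0.05 × 600 = 30 people, and the same reversal would remain.

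**What to change.** Delete the below-5% trigger, or reverse it. State that at 5% or more (or, more simply, at any level of missingness) the primary GEE analysis includes all randomised participants through multiple imputation that respects the CBS-group clustering. Add a sensitivity analysis for data missing not at random. State also that participants who stop attending sessions will still be surveyed at both endlines, so that session dropout does not turn into missing outcomes by default. If a threshold is kept, say whether it applies overall, per arm or per variable.

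The detailed list of imputation variables can be left to the SAP. Replacing the GEE with a mixed model is optional and not needed to resolve this point.

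The cost is a short wording change and a little more analysis work. The sample size does not change. Surveying session dropouts is already implied by intention to treat.

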## Plans to give access to the full protocol, participant-level data, and statistical code

There are no plans for granting public access to the full protocol, participant-level dataset, and statistical code beyond the publication of this protocol.

### Adverse event reporting and harms

There is no known adverse event or harm associated with participating in this study. Nevertheless, given that this study is being carried out in a post-genocide context, we could expect participants to experience emotional distress. Therefore, any adverse events that might arise during the conduct of this trial will be duly recorded by data collectors, who will thereafter report to field leaders. This will lead to immediate follow-up by a team of clinical psychologists who are on site and will provide psychological support when needed.

### Plans for communicating important protocol amendments to relevant parties

All protocol amendments will be reviewed and approved by the Institution Review Board of the College of Medicine and Health Sciences for prior approval or notification. The Principal Investigator will sign and date the approved protocol amendment before implementation. Any departures from the protocol will be documented in the participant file.

#### Dissemination plans

Planned publications in high-impact peer-reviewed journals. We will also disseminate locally at community and policy levels. And we provide detailed feedback to CBS. Participant-level dataset and statistical codes will be made available on reasonable request from the principal investigator.

#### Trial status

This is the original version of the protocol, issued in April 2022. The recruitment phase is planned to start in July 2022 and end approximately by August 2022. Any changes or protocol amendments will be accounted for in the public study record available on clinical trials. gov with ID: ISRCTN11199072.

## Discussion

This is the first study that evaluates the effectiveness of CBS on social dignity among its participants, including genocide perpetrators, survivors, their descendants, people in conflicts (family/community), and local leaders. This represents an ecologically valid approach as the primary outcome variable is the result of qualitative work with CBS experts which lead to the conclusion that this outcome best describes the true impact CBS intends to have (and drives secondary outcomes). Compelling evidence shows that CBS contributes to improved mental well-being, social connections, restorative justice, healing and reconciliation, increased trust and social capital, reduction of partner violence, active civic participation, improved economic development, and peacebuilding [28, 29, 49]. The proposed study will allow us to obtain a deeper understanding of the effectiveness of CBS on a psychometrically validated measure that reflects the functioning of CBS as understood by CBS experts, and will help us understand how this impact relates to secondary which are well-established and theoretically founded. Concretely, this study will allow us to measure the effectiveness of CBS among individuals dealing with the consequences of the 1994 genocide against the Tutsi on social dignity and related secondary outcomes. We hypothesize that participants in the intervention group will show improved social dignity and secondary outcomes compared to those in the control groups.

More broadly, this study could inform CBS implementers, policymakers, and other stakeholders and practitioners on the role of social dignity in interventions that focus on psychosocial healing interventions.

## Data Availability

The final data set for the proposed study will be available upon reasonable request from the corresponding author.
